**Research Protocol**

Synopsis

This pragmatic trial with cluster randomization of AEDs is designed to evaluate the effectiveness and cost-effectiveness of screening methods (modified PAT vs FAST vs modified SASQ) and interventions (Leaflet vs Brief advice vs Brief counselling) in routine AED care. Due to the design implications of a multi-level factorial design in AEDs the proposed trial involves a universal screening approach in which relevant data for a sub-sample of linked presentation population is collected. Therefore, the trial design encompasses a 3x3 factorial trial, screening method (modified PAT vs FAST vs modified SASQ) and intervention (Leaflet vs Brief advice vs Brief lifestyle counselling). The main advantages of utilising a factorial approach are twofold. First each of the three elements (screening tool and intervention) can be analysed independently with sufficient power to make meaningful interpretation of relative effectiveness. Second, the method enables meaningful interpretations of the relative effectiveness of any combination of screening method and intervention. Because the universal screening population encompasses a sub-group of linked presentation targeted population we can make meaningful comparisons of the relative effectiveness and interactions associated with screening approach in AEDs. Nine AEDs across the North East, London and the South East Regions of England will be recruited. AEDs will be randomly allocated to one of three intervention conditions: the patient information leaflet control condition (n=3), the structured brief advice condition (n=3); and lifestyle counselling by an Alcohol Health Worker (n=3). To test the relative effectiveness of different screening methods all AEDs will be randomised to either a modified single item screen (Single Alcohol Screening Question; M-SASQ) or a modified Paddington Alcohol Test (SIPS-PAT) or FAST Alcohol Screening Test (FAST) screening method. AEDs in the modified PAT condition will use targeted screening as per the standard PAT protocol. AEDs in the FAST and modified SASQ conditions will use universal screening for case identification and collect information about whether a patient would be part of a linked presentation group and then use statistical simulation to analyse any interactions. Screening randomisation will be stratified by median AED admission rates (2 levels) and intervention condition (3 levels). Each AED will recruit a minimum of 131 patients who are hazardous or harmful drinkers into the trial and a short baseline assessment will be carried out. Outcome will be assessed at 6, and 12 months after intervention. Outcomes will include system implementation outcomes and patient outcomes. We will also examine the practitioner and organisational factors associated with successful implementation.

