Nine AEDs in three English regions (North East, London, South East) will be recruited to take part in the study. Recruitment will take place with the assistance of the British Association of Accident and Emergency Medicine (BAEM, of which [name] is a Professor of Accident and Emergency Medicine and adviser to BAEM on the management of alcohol misuse). All AEDs in the three regions that do not have current routine alcohol screening and brief intervention facilities will be eligible to participate. AEDs will be selected to provide a range of both urban and rural catchment areas.

Design

AEDs will be randomly allocated to one of three implementation conditions (leaflet, brief advice or brief lifestyle counseling intervention) in a cluster randomized design such that there will be 3 AEDs in each condition. AEDs will be randomized to one of three screening conditions (described below) such that there will be 3 AEDs in each condition (see Table **1**). Patients enrolled in the study will have a baseline research assessment carried out by structured interview, and followed in parallel groups over 6, and 12 months. Outcome assessment will be by face to face or telephone interview conducted by a researcher.

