However, it is unclear which approach is most effective in identifying cases in the typical AED setting. The modified PAT (SIPS-PAT) is a targeted screening tool which is applied in cases with presenting conditions commonly associated with alcohol misuse. The original PAT has been used at St Mary’s Hospital embedded in the standard clinical assessment process. SASQ on the other hand has been studied in PHC and, based on our pilot research, is more likely to be adopted by busy AED staff. The FAST has been used mainly in a research screening context to establish prevalence rather than as a clinical tool. Also this single question in the modified SASQ will identify individuals whose level of drinking is more likely to lead to AED attendance, and is the same first item of the FAST questionnaire, which was found to identify 50% of hazardous and harmful drinkers (Hodgson et al., 2002).

Brief intervention implementation conditions

1. *Control condition:* AED staff (including dedicated AHWs) in the control condition will be trained to apply the appropriate screening method and record the screening outcome, will feedback the result of screening to patients and offer them a patient information leaflet (PIL. The PIL from the Drink-Less Programme and has been extensively pre-tested with clinicians and patients in PHC and will be used in this trial. The PIL will also contain a number for Drinkline where the patient can access further information). The PIL to be used in this trial will be ‘Alcohol and Sensible Drinking’ as in the PHC study.

2. *Brief Advice condition:* AED staff (including dedicated AHWs)will be trained to carry out screening and deliver up to 5 minutes of simple structured brief advice for hazardous and harmful drinkers presenting to the AED, using the Drink-Less brief intervention materials (level 1) as in the PHC study. Patients in this condition will also receive a Patient Information Leaflet (PIL) as above, including a number for Drinkline.

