In the Brief Lifestyle Counselling condition the training and support for AED staff will be the same as in the simple structured advice condition except that staff will be trained to screen and refer to the AHW. The equivalent of approximately 0.5 WTE AHW salary per AED has been allocated. In some areas it may be more practical to have one AHW split between two AEDs. In other areas different configurations can apply. The AHW will be responsible for training and supporting the AED staff in implementing screening and referral over the course of the project. The AED staff will also be supported in implementation of the screening and research procedures by a member of the research team.

Inclusion criteria

AEDs: Eligible AEDs will be those not already providing routine screening and SBI.

Patients: Any AED patients scoring positive on the modified PAT, FAST or modified SASQ aged 18 or over, and who are alert and orientated, resident within 20 miles and able to speak, read and write English sufficiently well to complete study questionnaires.

Exclusion criteria

Those who are currently seeking help for alcohol problems and those who are involved in any alcohol research study will be excluded. Any patients within the AED setting who are severely injured, suffering with a serious mental health problem and/or who are grossly intoxicated will also be excluded from the study. Finally patients with no fixed abode will be excluded from the study.

Consent

Consent to participate will be obtained in a 2 stage process. AED staff (including dedicated AHWs) will initially establish verbal consent to be check eligibility to take part, collect some basic demographic information and to be screened. Those who then are positive on FAST or modified SASQ or SIPS-PAT as applicable, will have the study explained to them verbally by AED staff (including dedicated AHWs) and in writing (using the patient information sheet). Written informed consent will be obtained by AED staff (including dedicated AHWs). This will include permission to give the patient's data and contact details to the research staff, and provide the research team with access to the patients AED records, and to participate in follow up after 6, and 12 months. The research team will then contact the patient within two weeks to thank him/her to take part in the study.

Measures

Staff attitudinal and organisational measures:

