The sample size calculation is designed to account primarily for intervention level outcomes. Powering the study in this way will also account statistically for appropriate outcomes for screening approach and screening method. The primary outcome for this study is the proportion of patients who consume alcohol within recommended levels at 6 month follow up. Recent meta-analysis (Moyer et al 2002) suggest that the difference between brief intervention and control is of the order 13%, 5% reduction in the control group and 18% in the brief intervention group. In order to detect a difference of this magnitude at the 5% significance level with 80% power, for a 2-sided test, requires 109 patients in each of the 3 groups, a total of 327. Our experience with other multi-centre randomized controlled trials of interventions for alcohol use disorders suggests that with assiduous follow-up the potential loss to follow-up across groups is of the order 25%. Taking this loss into accounts inflates the sample required to 131 in each group, a total of 393 patients per intervention.

The proposed study involves a cluster design and requires a statistical adjustment to account for any potential cluster effect. The literature, and our previous experience of trials in primary care, suggest an intra-class correlation coefficient of 0.04 is appropriate. Assuming a cluster size of the order 131 patients this inflates the sample size calculation by a factor of 2.7 requiring patients 393 in each group, a total of 1179, with an expectation that at least 882 will be followed up at 6 months.

We propose to recruit 9 AED’s. AED populations will be screened using 1 of 3 screening method groups (3 AED’s in each group) and will receive 1 of 3 intervention (3 AED’s in each group).

Planned analysis

As the study is pragmatic in design, the planned analysis will be by intention to treat. The primary outcome is dichotomous in nature, drinking within or above recommended levels, and will be analysed logistic regression adjusting for all known prognostic factors, data will be presented as odds ratios and their corresponding confidence intervals. Secondary analyses will be undertaken using the appropriate method for the outcomes, controlling where appropriate for intake values and other known prognostic variables using analysis of covariance. Simulations will be undertaken to encompass both screening approach groups and intention to treat analysis will be undertaken on both groups.

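### The allocated screening tool decides who is enrolled, so patient outcomes by screening tool or approach are not a randomised comparison, and the protocol's claims for screening go too far

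*Protocol*

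**What the plan says.** **Allocation and entry.** Under Design, "AEDs will be randomized to one of three screening conditions". Under Consent, the patients to whom the study is explained and who are asked for written consent are "Those who then are positive on FAST or modified SASQ or SIPS-PAT as applicable". The Inclusion criteria agree: "Any AED patients scoring positive on the modified PAT, FAST or modified SASQ aged 18 or over". The Synopsis adds that "AEDs in the modified PAT condition will use targeted screening as per the standard PAT protocol", while FAST and M-SASQ AEDs screen universally. Under Screening conditions, SIPS-PAT "is a targeted screening tool which is applied in cases with presenting conditions commonly associated with alcohol misuse".

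**Claims for screening.** The Synopsis presents the trial as an evaluation of the effectiveness and cost-effectiveness of screening methods as well as interventions. It says that each element "can be analysed independently with sufficient power to make meaningful interpretation of relative effectiveness", and makes a similar claim for every pairing of a tool with an intervention. The Sample size calculation is built on drinking within recommended limits at 6 months, and then states: "Powering the study in this way will also account statistically for appropriate outcomes for screening approach and screening method".

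**Analysis.** Planned analysis describes logistic regression for the drinking outcome and covariance analysis for secondary outcomes. It then says: "Simulations will be undertaken to encompass both screening approach groups and intention to treat analysis will be undertaken on both groups".

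**The concern.** For the screening factor, being in the analysed set is a result of the allocation. An AED given a different tool would have enrolled different patients, who could differ in drinking level and in reason for attendance. A comparison of their later drinking by tool or approach mixes any effect of screening with the selection made by the tool. Calling it intention to treat would credit it with a protection that it does not have.

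At stake is how the screening results are read. A tool that enrols milder drinkers could show more patients within limits at 6 months, and so look like the better screening method, without having changed anyone's drinking.

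**Working it through.** **Step 1: who is in each screening group.**

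| Tool (randomised by AED) | Who is screened | Who is enrolled |
|---|---|---|
| FAST | all attenders | FAST positives |
| M-SASQ | all attenders | M-SASQ positives |
| SIPS-PAT | alcohol-linked presentations | SIPS-PAT positives |

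Both the screened set and the rule for a positive result depend on the allocation. The protocol itself indicates that the tools select differently. Under Screening conditions, the M-SASQ question is described as the first FAST item, which found 50% of hazardous and harmful drinkers in the cited study. A set fixed independently of the screening allocation would be all eligible adult attenders, but 6-month drinking is followed up only in enrolled patients.

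**Step 2: do the stated safeguards restore comparability?**
- The flag for linked presentations in the universal AEDs can at best match them to the SIPS-PAT AEDs on type of presentation. It cannot match different questions and cut-offs, and restricting on it is an observational adjustment.
- The simulation is not described in the protocol. Its details may sit elsewhere, but simulation cannot turn selected groups into randomised ones.
- Adjustment for known prognostic factors does not restore randomisation.
- Baseline AUDIT is to be used to check matching between the intervention groups; no such check is mentioned for the screening groups.

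**Step 3: what the sample size was built on.** The inputs are 5% versus 18%, two-sided 5%, 80% power. With mean proportion 0.115 and difference 0.13:

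n = [1.96 × √(2 × 0.115 × 0.885) + 0.842 × √(0.05 × 0.95 + 0.18 × 0.82)]² / 0.13² ≈ 93.3, rounded up to 94.

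With the Fleiss continuity correction, (n/4) × [1 + √(1 + 4/(n × 0.13))]² ≈ 108.2, rounded up to 109. The plan's 109 per group is reproduced. Every input describes brief intervention against control on patient drinking; none concerns screening. Table 1 gives each screening method the same margin as each intervention (3 AEDs, 393 patients), but equal numbers do not make the screening groups comparable.

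**Step 4: possible size of the bias.** The documents give no case-mix by tool, so all values here are assumptions. Suppose the tool has no effect, a proportion s of enrolled patients are more severe drinkers, and the 6-month success rates are a in milder and b in more severe drinkers. The group rate is s × b + (1 − s) × a, so the spurious difference between two tools is (s₂ − s₁) × (a − b).

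| a, b | s = 50% v 70% | s = 40% v 80% |
|---|---|---|
| 20%, 10% | 15% v 13%: 2 points | 16% v 12%: 4 points |
| 25%, 5% | 15% v 11%: 4 points | 17% v 9%: 8 points |
| 30%, 5% | 17.5% v 12.5%: 5 points | 20% v 10%: 10 points |

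The range is 2 to 10 points, against a design difference of 18 − 5 = 13. With a − b = 25 points, the bias would reach 13 only if s differed by 0.13/0.25 = 52 percentage points. Sample size does not appear in the formula, so recruiting more patients does not reduce the bias.

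**Step 5: where the problem does not apply.** In Table 1 each intervention arm has one FAST, one M-SASQ and one SIPS-PAT AED, with 131 patients planned in each, so the tools are balanced across interventions. Under System measures, counts of patients screened, positive and treated can be set against all adult attenders, a denominator that the tool does not define. The proportion positive among those screened is less clean, because targeting decides who is screened.

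**The case against.** The strongest reply is that the protocol may not intend a comparison of patient outcomes between screening groups at all. The sentence in Planned analysis says that the analysis is done on both groups, which can mean the intervention comparison run within each screening approach. That would be legitimate. Elsewhere, screening effectiveness mostly means identification and activity: the last hypothesis concerns screening activity, Screening conditions speaks of identifying drinkers or cases, and System measures compares screening, conversion and intervention rates between tools. On this view, the outcomes that the power sentence calls appropriate for screening are these.

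Much of this stands. A reader might infer that the plan firmly commits to an invalid intention-to-treat contrast; the sentence is ambiguous and does not show that. A reader might also infer that the intended guideline on targeted screening would rest on biased 6-month drinking. The Design section bases it on the randomisation to targeted or universal screening and on the presenting conditions and demographic factors associated with positive cases. It does not mention 6-month drinking.

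The reply does not dispose of the Synopsis. That text claims effectiveness and cost-effectiveness for screening methods, and relative effectiveness for tool–intervention pairings, which is hard to read as case identification alone. Nor does it explain how a calculation on patient drinking secures power for identification measures.

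**Conclusion.** The concern holds in a limited form. Enrolment follows from the randomised tool and, for SIPS-PAT, from the presenting condition. Enrolled patients' drinking or cost-effectiveness by tool or approach is therefore not a randomised intention-to-treat comparison. The Synopsis and the Sample size calculation claim more for screening than the design can give, and the intention-to-treat sentence leaves room for the wrong analysis.

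The size is unknown. The 2 to 10 points rest wholly on assumed case-mix and success rates. More extreme assumptions give more, but nothing in the documents supports a claim that the bias would exceed the 13-point design difference. The intervention comparison is not undermined in this way, and neither are the system measures over all adult attenders. The protocol wording should change; the design need not.

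**What to change.** In the Synopsis, Sample size calculation and Planned analysis:

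- Limit randomised conclusions on screening method and approach to identification and activity measures, preferably with all adult attenders as the denominator.
- State that intention to treat applies to the intervention comparison, overall and within each screening-approach group. By Table 1, the targeted group has one AED per intervention and the universal group two, so the within-approach results need a caution.
- Label enrolled patients' outcomes by tool or approach as descriptive or adjusted observational, and show them with baseline AUDIT.
- Keep screening method in the outcome model as a design factor.
- Withdraw the power and relative-effectiveness statements as far as they concern patient outcomes by screening.

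The cost is wording only; no AED, patient or measurement changes. The sponsor gives up a claim that the design cannot support.
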